### The main study indicators and instructions

#### Independent variables: Antibiotic and probiotic use

To assess antibiotic and probiotic exposure, the information is recorded in detail through the HIS of the hospital including the dose, timing, duration, and type, which are collected not only in the perinatal period but also in the follow-up period. We enquire about maternal or infant administered medications such as antibiotics or probiotics by questionnaire, with the analysis from both simultaneous and separate perspectives to further clarify the effect on the periods of maternal and early life.

#### Outcomes of interest: Birth outcomes and early health outcomes

Birth outcomes include gestational age at delivery (weeks), mode of delivery (vaginal delivery or C-section), gender, infant Apgar scores, infant anthropometric measurements, and medications. The adverse birth outcomes are as follows [37]:A low Apgar score is defined as an Apgar score at 5 min of < 7.Low birth weight is defined as a live birth weighing < 2500 g.Small for gestational age infant (SGA) is defined as birthweight < 10% of that for a specific gestational age.Preterm birth is defined as a neonate born before 37 completed weeks.

The secondary health outcomes include antibiotic resistance, disease and treatments, physical development, and cognitive development, and they are recorded at every timepoint.Antibiotic resistance: It is reported that antibiotic resistance genes were found in infant faecal samples regardless of antibiotic exposure. In the study, we use 16S rRNA microbiome high-throughput sequencing and qPCR of ARGs for antibiotic resistance gene analysis.Disease and treatment: Common diseases in children often occur in the respiratory, digestive, or urinary systems, and the medical treatment and drug history are extracted from the HIS in the hospital.Physical development: Anthropometric measurements including weight (kg), height (cm), head circumference (cm), chest circumference (cm), and mid-upper arm circumference (cm), are standardized using WHO norms [37, 38].Cognitive development is assessed by standard Bayley Scales of Infant and Toddler Development (Bayley-IV), which is a widely used, comprehensive assessment of development for infants and toddlers aged 1 to 42 months [39] administered by trained research assistants.

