Probiotics are commonly used in paediatrics and even within families to regulate gut function. Probiotics are commonly defined as “live microorganisms which, when administered in adequate amounts, confer a health benefit to the host” [25]. The Food and Agriculture Organization/World Health Organization (FAO/WHO) consultation indicated that the potential health benefit is dose-based, however, the “adequate amount” in the definition is required to assess human interventions especially in early life periods. Although encouraging, existing conclusions are preliminary without longitudinal verification, and the reasoning behind using probiotics to deal with antibiotic resistance needs more evidence [26, 27].

Improper use of antibiotics and/or probiotics contributes to the development of antibiotic resistance. The strong influence of the infant resistome is mainly through the gut, oral cavity, vagina, and breastmilk, which enrich ARGs [28]. Additionally, some probiotic strains already have natural or mutant antibiotic resistance, and consumption may help restore gut microbiota imbalance caused by antibiotic treatment; however, some specific ARGs can be transmitted vertically, e.g., maternal microbial reservoir transmission during the vaginal delivery period to the infants. Moreover, strains could transfer antibiotic resistance to pathogenic microorganisms and other gastrointestinal commensal microorganisms through horizontal transmission [29]. Combining probiotics with antibiotics can reduce the incidence and severity of antibiotic-associated diarrhoea (AAD), so some special probiotics that do not carry resistance genes are selected to treat or prevent antibiotic side-effects [30]. However, the influence of vertically and horizontally transmitted aberrant microbiota on infants needs more evidence.

To address these issues, the Pregnancy and Birth Cohort in Northwest China (PBCC) was established to (a) clarify the association among antibiotic and probiotic exposure in early life, the microecology of the gut microbiota, and the development of antibiotic resistance; (b) investigate the long-term impact of antibiotics and probiotics on the health outcomes (including birth outcome, physical and cognitive development, disease and immune response) of infants and young children; and (c) provide a theoretical basis for the rational use of antibiotics and probiotics from a life course perspective.

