#### Delivery/birth outcomes

After delivery, the delivery record and birth outcomes will be collected by the staff. The meconium will be collected within 3 days (T4 in Fig. 1); most of the meconium samples are the first faeces, and all samples are from the first three bowel movements.

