### Biological sample collection and analysis

Faecal samples will be collected in three stages (shown in Table 1). The sample collection and laboratory experiments are as follows:

*Collection and preservation of samples for microbial testing*

We use a one-time sterile collection tube to collect fresh faecal samples with a 75% alcohol-disinfected stencil-sealed cover, which will be transferred quickly within two hours (using an icebox for temporary storage) to the hospital’s clinical laboratory and preserved in a -20 °C refrigerator and frozen after marking. Then, every two weeks, these samples will be temporarily transferred to a mobile fridge, with an average travel time of 60 min, ranging from 30 to 120 min to the lab located at Xi'an Jiaotong University, School of Public Health Centre. All the samples will be stored in a -80 °C refrigerator.

*DNA extraction and 16S rRNA gene amplicon sequencing*

Bacterial DNA is extracted from faecal samples with a QIAamp Fast DNA Stool Mini Kit (Qiagen, Cat. No./ID: 51,604), and PCR amplification is conducted with barcode-specific bacterial primers targeting the variable regions V3-V4 of the 16S rRNA gene: the forward primer 341F for 5′-CCTAYGGGRBGCASCAG-3’ and 806R for 5′-GGACTACNNGGGTATCTAAT-3’ [34]. Sequencing libraries and paired-end reads are generated on an Illumina HiSeq 2500 platform from Biomarker Technologies Co.Ltd. (Beijing, China) according to a standard protocol.

*ARGs detected by qPCR*

We then use quantitative PCR (*qPCR*) to detect the expression of ARGs in faecal samples. After a careful literature review, we selected 6 ARGs of four kinds of antibiotics: beta-lactam, tetracycline, fluoroquinolone, and macrolide, which are commonly used during pregnancy and early life [12, 35, 36]. Each sample includes three replicates for data accuracy.

**Table 1 Tab1:** Faecal sample collection at every timepoint of the Pregnancy and Birth Cohort in Northwest China (PBCC)

Stage	Timepoints	Period	Faecal sample	Sample source
Pregnancy	T1	1^st^ trimester	√	
	T2	2^nd^ trimester	√	Mother
	T3	3^rd^ trimester	√	
Delivery	T4	Birth	√	Infant
After birth	T5	42 days	√	
	T6	3 months	√	
	T7	6 months	√	Infant
	T8	12 months	√	
	T9	18 months	√	
	T10	24 months	√	

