For *q*PCR data, parametric repeated tests such as ANOVA determine different groups over time, and nonparametric tests after transformation to log10 such as t tests are used for analysis.

All analyses are performed using Stata v.13.1 (StataCorp, College Station, TX), and visualization is performed using R statistical software v3.6.1 (http://www.r-project.org/) with the ggplot2 package. Statistical significance is evaluated using a 95% confidence interval and a two-tailed *p value* of < 0.05.

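### The ANOVA and t tests named for the qPCR resistance-gene data adjust for no confounder and leave the mother's gene level out, although exposure is not randomised and maternal and birth samples are collected

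*Protocol article*

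**What the plan says.** The first aim (Background) is to "clarify the association among antibiotic and probiotic exposure in early life, the microecology of the gut microbiota, and the development of antibiotic resistance". ARGs are measured by qPCR: "we selected 6 ARGs of four kinds of antibiotics: beta-lactam, tetracycline, fluoroquinolone, and macrolide" (Biological sample collection and analysis).

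Two statements bear on what an infant carries before any treatment of its own. Under Outcomes of interest, the article reports that "antibiotic resistance genes were found in infant faecal samples regardless of antibiotic exposure". In the Background it says that "some specific ARGs can be transmitted vertically, e.g., maternal microbial reservoir transmission during the vaginal delivery period to the infants".

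Table 1 lists maternal stool in each trimester (T1-T3) and infant samples from birth (T4) to 24 months (T10). Of the birth sample the article says: "The meconium will be collected within 3 days (T4 in Fig. 1").

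For the qPCR data, Data management and statistical analysis says that "parametric repeated tests such as ANOVA determine different groups over time", and adds t tests on log10-transformed values. It names no covariate. Multivariable adjustment for confounders and linear or multilevel mixed models do appear in that section, as items (4) and (5) of the list introduced for the 16S rRNA sequence data.

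**The concern.** This is an observational cohort. Whether an infant receives antibiotics or probiotics is decided by illness, families and clinicians, not by allocation. By the article's own account an infant may carry ARGs without exposure, and some may come from the mother. If infants who are treated later already differ in ARG level, an unadjusted group comparison attributes that difference to the treatment.

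ARG level is the direct measure of resistance in the first aim, and the results are meant to inform rational-use strategies. The samples that could separate earlier carriage from later change are already scheduled. The tests named for these data do not use the maternal samples, and they do not condition on the level at birth.

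**Working it through.** **1. What each analysis can do.**

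| Data | Named method | Confounder adjustment | Within-child modelling | Maternal level |
|---|---|---|---|---|
| 16S | Multivariable analysis; mixed models | Yes, item (4) | Yes, item (5) | Mother-infant microbiota mentioned in item (4) |
| qPCR ARGs | Repeated ANOVA; t tests on log10 | None named | Repeated tests over time | None named |

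A t test cannot adjust for anything. A repeated ANOVA takes the child's earlier samples as outcomes but does not condition on them, and the mother's level does not enter.

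**2. Group size used for scale.** The article sizes the study on antibiotic-associated diarrhoea (AAD), not on ARGs. Its 354 per group reproduces with p0 = 0.25 (the lower end of its 25%-53% range), RR = 0.61, 90% power and two-sided 5%:

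- p1 = 0.61 × 0.25 = 0.1525; mean p = 0.20125
- n = (1.960 × √0.3215 + 1.282 × √0.3167)² / 0.0975² = 353.3, rounded up to 354

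The figure is borrowed below only to give a standard error. It is not an ARG exposure-group size.

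**3. Bias under stated assumptions.** Let rho be the correlation between the earlier (maternal or birth) and the later log10 ARG level, and d the difference in earlier level between exposure groups in SD units. Assume no true exposure effect and no other path.

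- Bias of the unadjusted comparison = rho × d
- Smallest: 0.2 × 0.1 = 0.02 SD. Largest: 0.7 × 0.3 = 0.21 SD.
- SE = √(2/354) = 0.0752 SD
- Rejection rate = 1 − Φ(1.96 − bias/SE) + Φ(−1.96 − bias/SE)

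| rho | d = 0.1 | d = 0.2 | d = 0.3 |
|---|---|---|---|
| 0.2 | 5.8% | 8.3% | 12.6% |
| 0.3 | 6.8% | 12.6% | 22.4% |
| 0.5 | 10.2% | 26.5% | 51.4% |
| 0.7 | 15.4% | 46.1% | 79.8% |

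The nominal rate is 5%. The article gives no ARG mean, SD or correlation, so rho and d are assumptions throughout.

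**4. Precision.** Adjusting for the earlier level leaves a fraction 1 − rho² of the residual variance: 0.96 at rho = 0.2 and 0.51 at rho = 0.7. The cut is therefore 4% to 49%.

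**The case against.** **A condensed article leaves covariate lists to the full plan, and the tests are given as examples.** This is fair as far as it goes; a missing covariate list would be no finding. But the article does state adjustment and mixed models for the 16S data, then gives the qPCR data a separate paragraph with simpler tests. The point is the method that is named.

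**The Outcomes section assigns both 16S sequencing and qPCR to resistance-gene analysis, so the 16S adjustment might carry over.** It might be meant to. As written, items (4) and (5) concern microbiota abundance, diversity and change, not gene levels. This does rule out saying that the mother-child pairing goes unused in the plan as a whole.

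**A reader might infer that the child's own earlier level is ignored.** The text does not support that. Repeated tests over time include the child's earlier samples, and a group-by-time contrast starting at T4 would use the birth level. Such a contrast is not automatically unbiased, though. Under the assumptions above, a change score has bias d × (rho − 1), which at d = 0.3 runs from −0.24 SD (rho = 0.2) to −0.09 SD (rho = 0.7). The maternal level is still absent.

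**A reader might also infer that the bias makes antibiotics look as if they cause resistance.** That needs families with heavy antibiotic use to pass on more ARGs and to have infants who are treated more. The article says neither. It says only that some specific genes can be transmitted, and it does not rank inheritance among the predictors of later level.

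**T4 is not a guaranteed pre-exposure sample.** This stands. Meconium is taken up to 3 days after birth, NICU admission averages 10%, and preterm and intensive-care neonates are eligible. Nothing says when infant courses begin. T4 also follows any prenatal exposure.

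Finally, the qPCR paragraph speaks of groups without naming exposure. Comparison by exposure is inferred from the first aim.

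**Conclusion.** The point holds in this form: the tests named for the qPCR ARG data are unadjusted group comparisons that do not use the mother's level, in a non-randomised cohort whose own text gives reasons to expect carriage before treatment. A model using samples already scheduled would serve the aim better.

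The size is illustrative. Over the assumed ranges the bias runs from negligible (0.02 SD, about 6% rejection) to serious (0.21 SD, about 80%). No single cell of the table, including the 51% at rho = 0.5 and d = 0.3, should be quoted as the expected error rate. The direction cannot be determined from the article. Antibiotic resistance is listed among the secondary health outcomes, although it is part of the first aim, so the change is worth making but does not threaten the study as a whole.

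**What to change.** Replace the named qPCR tests with the type of mixed model already planned for the 16S data: log10 ARG level as outcome, child as random effect, and the measured confounders as covariates.

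- **Postnatal exposure:** model T5-T10, adding the same gene's level in the mother's last antenatal stool and in the child's T4 sample. Use T4 as the common baseline for treated and never-treated children, so that both groups have the same reference point. Flag infants exposed before T4, or exclude them in a sensitivity analysis.
- **Prenatal exposure:** do not adjust for a T3 or T4 sample taken after that exposure, because it may lie on the causal path. Use an earlier maternal sample from before the exposure where one exists. Women enter in any trimester, so sometimes none will.
- **Joint analyses of maternal and infant exposure:** apply the same rule to the prenatal term. In practice, report the prenatal effect from a model without post-exposure T3 or T4, and the postnatal effect from a model that includes them.

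The cost is a short paragraph of analysis text and no new samples or assays beyond those scheduled. Pairs without a T3 or T4 sample will need a stated method for missing covariates.

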### Research management

#### Follow-up compliance

Multiple strategies are used to improve the compliance of the women and infants: (1) Step-by-step training is carried out for the investigators to follow-up the participants. (2) Biological analysis reports are sent to the women regularly so that they can receive health information feedback in time. (3) Social media are used to keep in touch with the women. We use the WeChat application to set up a group to remind the participants of the date of follow-up and sample collection. (4) Calls and home visits are conducted for the participants who are not able to come to the health facilities.

#### Quality control

Regarding the design of the questionnaire, the literature had been extensively reviewed, advice had been obtained from obstetrics and paediatric experts, and preliminary interviews had been conducted before formal enrolment.

Regarding investigator training, everyone will receive a detailed workbook and guidance on how to complete a face-to-face questionnaire and call/home visit at the beginning. During the investigation, disagreements occurring between the two investigators will be resolved by a senior investigator.

After the regular investigation, researchers will check the questionnaire for missing data and logistical errors, and a supplementary survey will be conducted if needed. Data entry will be conducted by hard-copy questionnaire and online investigation, with double-entry assuring data accuracy.

### Data management and statistical analysis

Data will be collected and managed using REDCap (Research Electronic Data Capture) tools by investigators, and questionnaire data entry will be conducted as soon as possible at each timepoint. Moreover, the external data including the records from the HIS, will be inputted regularly. All pregnant women enrolled in the study will be included in the final analysis.

The characteristics of the women or infants are described as the means ± SDs or medians for quantitative variables and percentages with numbers for categorical variables. One-way ANOVA is used to test the difference in means for continuous variables, and chi-square tests or Fisher’s exact test are used to summarize the associations of categorical variables.

To analyse the 16S rRNA gene sequence data, we will not only perform cross-sectional comparisons across individuals at the same time but also perform longitudinal follow-up within the same individual at different time points. All the data will be analysed using QIIME tools. (1) For community diversity and dissimilarity, alpha-diversity metrics including diversity (Shannon, Simpson) and richness (Chao, ACE) are used to measure diversity within species, and beta-diversity metrics are employed using the Bray‒Curtis or binary Jaccard distance matrix to measure the differential abundance among species based on antibiotic exposure, probiotic consumption, delivery mode and feeding patterns. (2) Then, principal coordinate analysis (PCoA), nonmetric multidimensional scaling (NMDS), the unweighted pair-group method with arithmetic means (UPGMA) and heatmap of species clusters are used to conduct cluster and dimensionality reduction. (3) Furthermore, linear discriminant analysis (LDA) effect size (LEfSe), and Metastats methods are used to identify significant differences from the phylum to genus levels among groups. (4) Multivariable analysis is used to adjust for confounding factors and analyse the associations between clinical and microbiota data and identify the influencing factors of abundance and diversity of the mother-infant microbiota. (5) For longitudinal data analysis of gut microbiota changes over the first two years, a linear mixed effects model or multilevel mixed effects model are used. (6) A Dirichlet multinomial mixtures (DMM) model [40] is used for gut microbiota community type determination.

For *q*PCR data, parametric repeated tests such as ANOVA determine different groups over time, and nonparametric tests after transformation to log10 such as t tests are used for analysis.

All analyses are performed using Stata v.13.1 (StataCorp, College Station, TX), and visualization is performed using R statistical software v3.6.1 (http://www.r-project.org/) with the ggplot2 package. Statistical significance is evaluated using a 95% confidence interval and a two-tailed *p value* of < 0.05.

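### One uncorrected two-tailed p<0.05 rule covers the taxon-level and resistance-gene tests, with no multiplicity control and no stated precedence for the adjusted models

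*Protocol article*

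**What the plan says.** All of the following is in the Protocol article. Unless noted, it comes from Data management and statistical analysis.

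- **Decision rule.** After naming the software for all analyses, the section ends: "Statistical significance is evaluated using a 95% confidence interval and a two-tailed" p value below 0.05. No other threshold and no multiplicity procedure appears anywhere in the article.
- **Taxon tests, item (3) of the 16S plan.** LEfSe and "Metastats methods are used to identify significant differences from the phylum to genus levels among groups". No covariates are named in this item.
- **Grouping factors, item (1).** Diversity is compared "based on antibiotic exposure, probiotic consumption, delivery mode and feeding patterns".
- **Adjustment, item (4).** "Multivariable analysis is used to adjust for confounding factors and analyse the associations between clinical and microbiota data", and it is also meant to "identify the influencing factors of abundance and diversity of the mother-infant microbiota".
- **Longitudinal data, item (5).** For changes over the first two years, "a linear mixed effects model or multilevel mixed effects model are used".
- **Genes.** Under Biological sample collection and analysis, "we selected 6 ARGs of four kinds of antibiotics". For the qPCR data, "parametric repeated tests such as ANOVA determine different groups over time", with t tests also mentioned. No covariates are named.
- **Timepoints.** Table 1 lists ten faecal collections: three maternal (T1-T3) and seven from the infant (T4-T10).

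**The concern.** Aim (a) links antibiotic and probiotic exposure to the gut microbiota and to antibiotic resistance. The evidence for it will largely be a list of taxa and genes declared different between exposure groups. With one 5% threshold for each of many tests, part of that list is expected to be chance, and the reader cannot tell which part.

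A second problem is order of precedence. A taxon may be significant in the unadjusted item (3) comparison and null in the adjusted item (4) or (5) model, and the plan does not say which result counts. The gene results are more exposed still: items (4) and (5) belong to the 16S analysis, so as described the qPCR comparisons have neither multiplicity control nor adjustment.

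The Discussion in the abstract and the Implications section both say that the findings will inform antibiotic and probiotic use and strategies for practitioners and policy-makers. A list without error control is a weak basis for that.

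**Working it through.** **The plan's own use of 5%.** The sample size spends alpha = 0.05 on one comparison of antibiotic-associated diarrhoea risk. With p0 = 0.25 (the low end of the stated range), RR = 0.61, so p1 = 0.1525, two-tailed 5% and 90% power, the stated formula gives 354 per group, as printed. Then 354 × 1.2 = 424.8, rounded up to 425, and 425 × 2 groups × 3 districts = 2,550, also as printed. So the 5% level was planned for a single contrast. The point below does not touch the sample size.

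**Inputs for the gene family.** 6 ARGs (Biological sample collection and analysis); 7 infant timepoints (Table 1); 2 study exposures, antibiotics and probiotics; alpha = 0.05.

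**Formulas.** For m tests with every null true, expected false positives = 0.05 × m. If the tests are also independent, the chance of at least one = 1 − 0.95^m.

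| Reading of the plan | m | Expected false positives | Chance of at least one |
|---|---|---|---|
| Six genes, one contrast, one timepoint | 6 | 0.3 | 26.5% |
| One overall test per gene and exposure (6 × 2) | 12 | 0.6 | 46% |
| Six genes at each timepoint, one exposure (6 × 7) | 42 | 2.1 | 88.4% |
| Each timepoint, both exposures (6 × 7 × 2) | 84 | 4.2 | 98.7% |

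The article does not say whether genes get one test across time or one at each visit, so 12 and 84 bracket the plausible readings. Correlation between tests lowers the last column but not the expected counts.

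**Taxa.** The number tested is not given. The rule yields 0.05 × 100 = 5 false positives per 100 null taxa for each contrast. Taking 50 to 100 genera purely as an assumption, one contrast at one timepoint gives 2.5 to 5.

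**Does it follow that most significant results are chance?** The false share among significant results is 0.05·π0 / [0.05·π0 + power·(1 − π0)], where π0 is the proportion of true nulls. It passes 50% when π0 exceeds power/(power + 0.05):

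- power 30%: 0.30/0.35 = 86%
- power 50%: 0.50/0.55 = 91%
- power 80%: 0.80/0.85 = 94%
- power 90%: 0.90/0.95 = 95%

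At π0 = 80% and 80% power the share is 0.04/(0.04 + 0.16) = 20%. At π0 = 95% and 50% power it is 0.0475/(0.0475 + 0.025) = 66%. The documents give neither π0 nor power for these tests.

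**The case against.** **A condensed article may leave FDR control to an analysis plan that is not shown.** This is fair as far as silence goes, and absence alone would not be a finding. But the article is not silent: it states a general 0.05 rule and uses step (3) to declare significant differences. It is true that the sentence does not say whether raw or adjusted p-values are compared with 0.05. Nothing in the text points to adjusted ones.

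**Confounding is already dealt with.** A reader might infer that the taxon findings will simply mix exposure effects with those of delivery mode and feeding. The article does not support that. Item (4), directly after LEfSe/Metastats, plans adjustment for abundance and diversity, and item (5) plans mixed models. LEfSe and Metastats are one item of six and are nowhere called the final test. What stands is narrower: no precedence is given to the adjusted results, and both items sit under the 16S data, so they do not reach qPCR.

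**A missing child random effect.** This could be held against item (3), but comparisons at one timepoint use one planned sample per child, so there is no within-child correlation to model. Repeated data go to item (5). The criticism falls away.

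**Large counts of false taxa.** One could multiply an assumed 100 to 200 taxa by four factors and seven timepoints: 28 × 5 to 28 × 10 = 140 to 280. The taxon count is not in the article, the four factors are listed for the diversity metrics and not for item (3), and the product treats delivery mode and feeding as having no effect. That figure should not be used.

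**The 84 gene tests are one reading.** This is correct, and is why 12 is shown beside it. Even 12 tests leave a 46% chance of at least one false positive.

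**Conclusion.** The point holds in limited form. The article fixes one uncorrected 5% rule for families of taxon and gene tests. For the genes, on the article's own counts, this means between 0.6 expected false positives (46% chance of at least one, 12 tests) and 4.2 (98.7%, 84 tests). For taxa it means about 5 per 100 null taxa per contrast. The counts assume that all nulls are true; the percentages also assume independence.

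A reader might go further and conclude that most significant results will be chance. That would need roughly 86% to 95% of the tested nulls to be true, depending on power, and the documents give no basis for such a figure. Many can be chance; most is not shown.

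The adjustment problem is one of precedence for the 16S data and of coverage for the qPCR data. The change is worth making, but it alters neither the design nor the sample size.

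**What to change.** In Data management and statistical analysis:

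1. Replace the single threshold for these families. Declare taxon-level and ARG findings by Benjamini-Hochberg FDR at q<0.05. Define the families as taxa within taxonomic level and exposure contrast, and the six ARGs across timepoints and exposures together.
2. State that inference on taxa rests on the adjusted and mixed models already planned in items (4) and (5).
3. Extend the same confounder adjustment to the qPCR outcomes.
4. Label unadjusted LEfSe/Metastats results exploratory.

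The cost is a few sentences and routine software, with no new data. The downside is that fewer taxa and genes will be declared significant. With 84 gene tests, the Benjamini-Hochberg cut-off for the smallest p-value is 0.05/84 = 0.0006, and for the tenth smallest 10 × 0.05/84 = 0.006, so the loss is smaller when several genes show real differences.
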